## Abstract

**Background:**

Attention-deficit/hyperactivity disorder (ADHD) is a prevalent neurodevelopmental condition affecting approximately 7% to 8% of children and adolescents, characterized by persistent inattention, hyperactivity, and impulsivity. Adolescence represents a period of heightened vulnerability, during which pharmacological treatments are frequently limited by adverse effects, suboptimal adherence, and partial response. Physical exercise, particularly high-intensity interval training (HIIT), has demonstrated superior effects on inhibitory control and inattention compared with moderate-intensity continuous exercise. However, the repetitive nature and high perceived exertion of traditional HIIT protocols result in poor adherence, especially in individuals with ADHD. Virtual reality (VR)–based exergames have been proposed as a strategy to sustain vigorous physiological demands while maintaining intrinsic motivation. Despite this potential, the existing literature is predominantly limited by passive control conditions, which prevent adequate control for the effects of VR immersion and cognitive engagement, limiting causal inference regarding the specific contribution of physiological exertion.

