## Introduction

Attention-deficit/hyperactivity disorder (ADHD) is a prevalent neurodevelopmental condition that affects approximately 7% of children and adolescents worldwide and is associated with substantial academic, social, and functional impairment that often persists into adulthood [1,2]. Pharmacotherapy, particularly psychostimulants, remains a mainstay of treatment and is effective in reducing core symptoms [3,4]. However, functional impairments frequently persist, long-term academic and psychosocial benefits remain debated, and clinical utility is often limited by adverse effects and poor adherence during adolescence [3,5]. These limitations highlight the need for effective nonpharmacological interventions.

Physical exercise has emerged as a promising adjunctive strategy for youth with ADHD [6]. There is evidence suggesting that exercise interventions can improve specific executive function domains, particularly inhibitory control, as well as core symptoms such as inattention [7]. Nevertheless, adherence to high-intensity exercise protocols is often challenging, especially in adolescents, due to monotony and physical discomfort associated with vigorous exertion [8]. Exergaming, which integrates physical exercise with immersive digital environments, has been proposed as a means of combining physiological stimulation with enhanced engagement and motivation [9,10]. Virtual reality (VR)–based exergames in particular allow for the delivery of structured exercise protocols while maintaining high levels of user involvement.

Despite this potential, a key methodological limitation in the current literature is the difficulty of disentangling cognitive and behavioral effects attributable to physiological exertion from those related to the cognitive and motivational features of gaming and VR environments [9]. Many previous studies have relied on passive or nonequivalent control conditions, limiting causal inference regarding the specific contribution of exercise intensity [7].

To address this gap, this randomized clinical trial evaluates the effects of a high-intensity interval training (HIIT)–based VR exergame compared with an active, nonexercise VR control condition in adolescents with ADHD. The primary objective is to determine whether the HIIT-based VR intervention leads to greater improvements in inhibitory control and inattention than VR exposure without physical exertion.

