#### Control Condition (Nonexercise VR)

Participants assigned to the control group will use an adapted nonexercise version of Move Sapiens. This version preserves the same immersive VR environment, visual assets, and sound design but removes all components of physical exertion. Interaction occurs exclusively through a joystick. Session duration and frequency mirror those of the intervention group. This design enables examination of the specific contribution of vigorous physical exertion to the observed outcomes while controlling for VR immersion and digital engagement, both of which are preserved across conditions.

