### Sample Size

The sample size calculation assumed a statistical power of 0.80, a significance level of an α value of .05, and a medium effect size of 0.50, consistent with literature on exercise interventions in ADHD. Accounting for an expected attrition rate of 30%, the required total sample size is 98 participants, with 49 participants allocated to each study arm. We will balance recruitment across the 2 study sites.

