### Statistical Methods

All participants will be included in an intention-to-treat analysis. Continuous outcomes will be examined using linear mixed-effects models with random intercepts accounting for repeated measures and missing data. The models will include terms for treatment group, time (modeled as a continuous variable), and the treatment-by-time interaction to estimate differential change between groups. An autoregressive covariance structure will be applied to account for temporal correlation. Statistical significance will be defined as a 2-sided *P* value of less than .05. Between-group effect sizes will be estimated using the Cohen *d*. All analyses will be conducted using RStudio (Posit PBC).

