If the study demonstrates significant improvements in inhibitory control and inattention in the HIIT VR group compared with the nonexercise VR control, these findings will support the clinical efficacy of an HIIT-based VR exergame as a novel, engaging nonpharmacological intervention for adolescents with ADHD. Such results would have important implications for expanding treatment options in a population characterized by limited adherence to existing therapies. Conversely, if no differential effects are observed between groups, this would suggest that immersive VR engagement itself may represent a key therapeutic component, providing valuable insights for the design of future digital and game-based interventions. By evaluating a developmentally appropriate, home-based HIIT VR intervention within a rigorously controlled design, this trial has the potential to advance both the clinical and methodological evidence base for nonpharmacological treatments in ADHD. Results will be disseminated through peer-reviewed publications and scientific conferences regardless of the direction of the findings.

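### The 0.50 effect size is supported only by general ADHD exercise literature, not for exertion beyond an active VR game, so the 80% power rests on an effect not justified for this comparator

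*Protocol article*

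**What the plan says.** The Sample Size section gives a power of 0.80, an alpha of .05, 30% attrition and 98 participants (49 per arm). Its support for the effect is one phrase: "a medium effect size of 0.50, consistent with literature on exercise interventions in ADHD". It names no source, outcome, effect metric or comparator.

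The Introduction describes the earlier work: "Many previous studies have relied on passive or nonequivalent control conditions, limiting causal inference regarding the specific contribution of exercise intensity". The reference attached to that sentence is the one the Introduction also cites for exercise effects on inhibitory control and inattention. The Discussion again contrasts this trial's control with the passive or nonequivalent comparators often used before. The Abstract has a stronger phrase, "the existing literature is predominantly limited by passive control conditions", placed directly after its sentence on VR exergames.

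The control condition is of another kind: "This version preserves the same immersive VR environment, visual assets, and sound design but removes all components of physical exertion". Session length and frequency match the intervention arm.

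The Discussion also says in advance how it would read no difference between the arms: "this would suggest that immersive VR engagement itself may represent a key therapeutic component".

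**The concern.** The article gives weak comparators in earlier work as a reason for running the trial, then uses the exercise literature in general as the only support for its effect size. An effect against a passive control can include attention, novelty and engagement as well as exertion. This trial's control is built to keep VR immersion and digital engagement, so part of such an effect may cancel between the arms. An effect plausible against a passive control need not be plausible here.

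The stake is the reading of a null result. If the true added effect of exertion is below 0.50, the trial has less power than a reader of the Sample Size section would think. The planned reading would then turn a missed exertion effect into support for VR engagement.

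**Working it through.** **Inputs.** Power 0.80, alpha .05, d = 0.50, attrition 30% and 49 per arm come from the Sample Size section. The two-sided test comes from Statistical Methods. Completers per arm after attrition: 49 × 0.70 = 34.3, taken as 34. The article gives no effect against an active VR control, so the values below 0.50 are assumptions shown as a range.

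**The plan's own figure.** For a two-sided two-sample comparison, n per arm = 2(1.960 + 0.842)² / 0.50² = 62.8, so 63 (64 by t-test). That is 126 in total, and 63 / 0.70 = 90 per arm, or 180 in total, with attrition. The stated 98 is not reproduced. As a between-arm calculation it needs an unstated baseline–post correlation ρ:
- ANCOVA: 1 − ρ² = 34.3/63 = 0.544, so ρ ≈ 0.67.
- Change score: 2(1 − ρ) = 0.544, so ρ ≈ 0.73.

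A paired (within-group) t-test at 0.50 also leads there: 34 / 0.70 = 48.6, so 49. This mismatch is a separate matter. It matters here only because it decides which power figures apply, so both cases are shown.

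**Case A: plain two-sample t-test, no baseline adjustment.**

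| d (SD) | 49 per arm, no attrition | 34 per arm, 30% attrition |
|---|---|---|
| 0.50 | 69% | 53% |
| 0.45 | 60% | 45% |
| 0.40 | 50% | 37% |
| 0.35 | 40% | 30% |
| 0.30 | 31% | 23% |

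The effect detectable with 80% power is about 0.57 SD at 49 per arm and 0.69 SD at 34 per arm.

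**Case B: granting the plan exactly 80% at 0.50, by whatever method.** Power at a smaller d is approximately Φ(2.802 × d/0.50 − 1.960):
- d = 0.40: Φ(2.241 − 1.960) = Φ(0.281) = 61%
- d = 0.35: Φ(1.961 − 1.960) = 50%
- d = 0.30: Φ(1.681 − 1.960) = Φ(−0.279) = 39%

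**What belongs to this point.** In Case A, the fall from 80% to 69% or 53% at d = 0.50 comes from the sample size arithmetic, not from the comparator. The effect-size question is the fall down each column. Case B shows it alone: from 80% to 61% if the effect is 0.40, and to 39% if it is 0.30.

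**What a null would look like.** Without baseline adjustment, the 95% interval for the standardised difference at 34 per arm has a half-width of about 1.997 × √(2/34) = 0.48 SD. An observed difference of zero would still be compatible with an exertion effect of almost 0.5 SD.

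**The case against.** Four objections have force.

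- **Origin of 0.50.** The article says the value is consistent with the exercise literature, not that it was derived from passive-controlled trials. A reader might infer that it was, or that the article calls this literature mostly passive-controlled. Neither is supported. The Abstract's stronger phrase most naturally describes VR exergame studies. For exercise, the Introduction says only that many studies had passive or nonequivalent controls. What stands is narrower: the stated support does not address this comparator.
- **Meaning of 80%.** A reader might conclude that the stated power is wrong for this contrast because of the comparator. Power is conditional on the assumed d, whatever the control. Only the justification of 0.50 is in question.
- **Direction and size.** The article gives no attenuated effect, and some features could enlarge the contrast. The Discussion concedes that the arms differ in gross motor demand and task experience, and that parents, who rate one primary outcome, know the allocation. The Abstract also reports HIIT as superior to moderate continuous exercise. That comparison is with another exercise, carries no figure, and does not speak to a VR game without exertion. A smaller effect is plausible but not shown, so a non-significant result cannot be called likely.
- **Condensed article.** A full justification or power table may be in the full protocol or analysis plan. The point does not rest on that absence. It rests on the support the article does give and on the reading of a null to which it commits.

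**Conclusion.** The point holds as a mismatch between the stated support for 0.50 and the contrast under test. It does not show that 0.50 is wrong.

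If the effect against active VR were 0.30 to 0.40 (an assumption), power would be 39% to 61% even granting the plan its 80% at 0.50. For an unadjusted two-sample t-test it would be 31% to 50% with 49 per arm, and 23% to 37% with 34. A baseline–post correlation used in the analysis would raise the unadjusted figures, but it has to be stated. It would also be too favourable to say that only effects below about 0.5 SD could be missed, because the unadjusted detectable effect at 34 per arm is about 0.69 SD.

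The practical consequence is the Discussion's reading of a null, which the trial's precision may not support.

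**What to change.** **Sample Size section.** Present 0.50 as an assumed target difference against the active VR control, and stop offering the general exercise literature as its support. State power at the planned size after attrition for d from 0.30 to 0.50, with the effect detectable at 80% power (about 0.69 SD unadjusted at 34 per arm). If a baseline–post correlation is relied on, give its value and source, and compute these figures with it.

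**Discussion.** Replace the reading of no difference as a sign that VR engagement is therapeutic. Interpret the result through the confidence interval for the HIIT-minus-VR difference, and say that a moderate exertion effect could be missed.

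**Cost.** A few sentences and one short table, with no change in enrolment, procedures or analysis. The stated power becomes less favourable. The article reports 58 of 98 enrolled and no interim analysis, so the change can be made before results are known.

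### The stated inputs do not give 98 as the required size for the two-sided between-arm comparison; for d = 0.50 on the analysed scale, power after 30% attrition is about 53%, not 80%

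*Protocol article*

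**What the plan says.** The Sample Size section of the protocol article gives its inputs as "a statistical power of 0.80, a significance level of an α value of .05, and a medium effect size of 0.50" and its result as "Accounting for an expected attrition rate of 30%, the required total sample size is 98 participants, with 49 participants allocated to each study arm". It names no test, does not say whether 0.50 is a between-arm or a within-arm effect or which SD scales it, and gives no pre-post correlation. Its only support for the value is that it is "a medium effect size of 0.50, consistent with literature on exercise interventions in ADHD".

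Other sections define the comparison. Study Design and Setting describes a parallel-group 1:1 trial that aims to show superiority over control. Statistical Methods tests the treatment-by-time interaction, reports a between-group Cohen d, and sets the test level: "Statistical significance will be defined as a 2-sided *P* value of less than .05". The Outcomes overview gives two assessments, baseline and postintervention.

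**The concern.** The article does more than leave details out. It states that a particular set of inputs requires 98 participants, and a reader can check that. For a two-arm comparison at two-sided .05, an effect of 0.50 needs well over 98 evaluable participants before any allowance for attrition.

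The consequence goes beyond one paragraph. The Discussion says that if the arms do not differ, this would suggest that immersive VR engagement itself may be a key therapeutic component. That reading presumes that a real effect of the assumed size would probably have been detected. If power is near one half, a non-significant result says little about whether exertion adds anything.

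**Working it through.** **Inputs.** Power 0.80, alpha .05, effect 0.50, attrition 30%, N = 98 (Sample Size); two-sided test, interaction contrast, between-group Cohen d (Statistical Methods); 1:1 allocation (Randomization and Blinding); two assessments (Outcomes); 46 of 58 completed so far (Results).

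**1. Attempt to reproduce 98 as a between-arm size.**

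- Normal approximation: n per arm = 2(1.960 + 0.842)² / 0.50² = 62.8, so 63. The exact two-sample t test (noncentral t) gives 63.8, so 64.
- Evaluable total: 2 × 64 = 128.
- With 30% attrition: 64 / 0.7 = 91.4, so 92 per arm and 184 in total.

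The stated figure is 98, so it is not reproduced. A one-sided test does not recover it either: 51 evaluable per arm by the t test, hence 51 / 0.7 = 72.9, so 73 per arm (146).

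**2. Power with 98 randomised, d = 0.50 on the analysed scale.** Noncentrality = 0.50 × √(n/2), df = 2n − 2.

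| Evaluable per arm | Noncentrality | Power, two-sided .05 |
|---|---|---|
| 34 (49 × 0.7 = 34.3) | 2.06 | 0.53 |
| about 39 (49 × 0.793, completion so far) | 2.20 | 0.59 |
| 49 (no loss) | 2.47 | 0.69 |

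The d detectable with 80% power is 0.69 at 34 per arm and 0.57 at 49 per arm.

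**3. If 0.50 is scaled to the raw-score SD.** Power for the difference in change then depends on the pre-post correlation r. The article gives no r, so the values below are assumptions.

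- Completers, change score: effective d = 0.50 / √(2(1 − r)).
- Mixed model that keeps dropouts' baselines: variance of the mean change per arm, in squared-SD units, is (1 − r²)/34 + (1 − r)²/49.
- Baseline-adjusted completers: effective d = 0.50 / √(1 − r²).

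| r | Change score, 34 per arm | Mixed model, 34 of 49 with post data | Baseline-adjusted, 34 per arm |
|---|---|---|---|
| 0.3 | 0.40 | 0.44 | 0.57 |
| 0.5 | 0.53 | 0.56 | 0.65 |
| 0.7 | 0.75 | 0.77 | 0.81 |
| r needed for 80% | about 0.74 | about 0.72 | about 0.69 |

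**4. Where 98 might have come from (conjecture).** A paired t test at d = 0.50, two-sided .05 and 80% power needs 34, and 34 / 0.7 = 48.6, so 49. That equals the stated per-arm figure, but it powers a pre-post change within one group. A repeated-measures within-between interaction with f = 0.25 and r = 0.5 gives 34 in total, or 49 in total after attrition; it would give 98 only if a total were taken for a per-arm number. A repeated-measures between-factors ANOVA (f = 0.25, two measurements, correlation 0.5) gives power 0.81 at N = 98, but with no attrition and for a different contrast. Nothing below depends on which, if any, was used.

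**The case against.** The strongest defence is that the planned analysis is not a plain two-sample t test. It is a mixed model with a baseline measurement, and with a high enough pre-post correlation 98 would suffice for an effect on the raw-score scale. The article is a condensed account, and a correlation may be given in a fuller document. This stands in part. A reader might infer that the trial's power simply is 53%, and the article does not support that without qualification: 53% holds for d = 0.50 on the analysed scale, or for a change score when r happens to be 0.5. On the raw-SD scale the change-score figure runs from about 0.40 to 0.75 as r goes from 0.3 to 0.7. The defence still does not rescue the sentence as published, because it presents 98 as following from inputs that include no correlation.

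Retention so far is better than planned, at 79.3%, and some of those not counted as completers may still be in training. At that rate power is about 0.59 on the analysed scale, which tempers the figure without curing it.

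Three further inferences should be resisted.

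- That the authors used a paired t test. The match with 34 / 0.7 is exact after rounding up, but other routes also lead to 34 or 98, and the article names none.
- That 0.50 is too large because earlier trials had weaker comparators. The Introduction says "Many previous studies have relied on passive or nonequivalent control conditions, limiting causal inference", but the literature behind 0.50 is not identified in the Sample Size section, so its comparators cannot be checked and no smaller value can be derived from the article.
- That power is lower still because both primary outcomes must succeed. Neither the outcome sections nor Statistical Methods states such a rule.

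**Conclusion.** The point holds. For a two-sided between-arm d = 0.50 on the analysed scale, the stated inputs require 128 evaluable and 184 randomised, against the 98 stated. With 98 randomised and 30% lost, power is about 53%. Even with no loss it is 69%, so the shortfall does not come from the attrition allowance alone. The detectable effect at 80% power with 34 per arm is about d = 0.69.

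These figures assume equal arms, equal loss in both arms, a normally distributed outcome and a single test at .05. Under the other reading of 0.50 (raw-score SD), 98 is adequate only if the pre-post correlation is roughly 0.72 to 0.74, or about 0.69 with baseline adjustment. What can be said firmly is that the published inputs do not produce the published number and that the claimed 80% rests on an assumption not on the page. The article does not establish a single true power for the trial, nor the cause of the discrepancy.

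**What to change.** Rewrite the Sample Size paragraph for the test that will be run:

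- Name the test and the SD that scales the effect of 0.50.
- State that, with 98 randomised and 30% attrition (about 34 per arm), power is about 53% for d = 0.50 on the analysed scale, and that the difference detectable with 80% power is d of about 0.69.
- If a raw-SD effect and a pre-post correlation were intended, give the correlation, its source and the power that results under the planned model.
- Withdraw the statement that 98 is the size required for 80% power.

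In the Discussion, temper the planned reading of a null result: report the confidence interval for the between-arm difference, and do not take non-significance as evidence that exertion adds nothing beyond VR engagement.

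The cost is one paragraph and one sentence, with the analysis plan kept in step. Enrolment and conduct do not change, and the article reports that no interim analysis has been done, so the correction can be made before results are known. The downside is that the stated power becomes less favourable.

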### Randomization and Blinding

Group allocation will be performed using a random sequence with a 1:1 allocation ratio stratified by study site. The randomization sequence will be generated by an independent researcher not otherwise involved in the study. To ensure rigorous allocation concealment and maintain the integrity of the single-blind design, the research staff is functionally divided into 2 distinct units. The blinded team includes outcome assessors responsible for baseline and postintervention assessments, as well as the data analyst, who will work exclusively with coded datasets (group A and group B) to ensure analytic neutrality. These team members have no access to the randomization list. Conversely, the unblinded team handles technical setup, safety supervision during familiarization, and daily remote monitoring as these tasks require awareness of the assigned condition.

Participant blinding to the physical nature of the task (movement vs joystick) is not feasible due to inherent differences in motor engagement. To minimize expectancy bias, participants are informed using a standardized script that the study compares “two different virtual reality training approaches for attention” without explicit mention of hypotheses regarding exercise superiority.

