### Outcomes

#### Overview

We will assess outcomes at baseline (visit 1) and the postintervention time point (visit 5). The specific measures are categorized as follows (Table 1).

**Table 1 table1:** Summary of outcome measures.

Outcome domain			Instrument		Metric

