## Results

This trial is ongoing. Funding was granted in October 2024. Recruitment commenced in June 2024 across 2 sites: Hospital de Clínicas de Porto Alegre (Rio Grande do Sul) and Centro Escola de Especialidades Médicas (São Paulo). As of April 2026, 58 participants have been enrolled (n=35, 60.3% in Rio Grande do Sul and n=23, 39.7% in São Paulo), of whom 46 (79.3%) have completed the full intervention protocol. Data collection is expected to be completed by October 2026, with results anticipated by December 2026. No interim analyses have been conducted.

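### Randomisation is stratified by site but the named model terms omit site; if change differs by site, the standard error will be slightly too large (about 0–5%)

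*Protocol article*

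**What the plan says.** Under Randomization and Blinding, the Protocol article says: "Group allocation will be performed using a random sequence with a 1:1 allocation ratio stratified by study site". There are two sites.

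Under Statistical Methods, continuous outcomes are to be analysed with "linear mixed-effects models with random intercepts accounting for repeated measures and missing data". The fixed part is described as follows: "The models will include terms for treatment group, time (modeled as a continuous variable), and the treatment-by-time interaction to estimate differential change between groups". The section also sets an autoregressive covariance structure, a two-sided significance threshold and Cohen *d* as the effect-size measure. Site is not mentioned in that section. The random intercepts are tied to repeated measures, so they describe participants and not sites.

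Outcomes are measured twice, at visit 1 and visit 5 (Outcomes, Overview). Recruitment was meant to be balanced across sites; the count at April 2026 was "n=35, 60.3% in Rio Grande do Sul and n=23, 39.7% in São Paulo" (Results).

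**The concern.** When allocation is stratified on a factor, the arms are balanced on it by design, and the true sampling variance of the treatment contrast no longer contains that factor's contribution. A model without the factor does not know this. Any outcome variation that the factor explains stays in the residual, and the reported standard error is then larger than the true one. For that reason it is normal practice to carry a stratification factor into the primary model.

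Here the factor that governed randomisation is missing from a model description that is otherwise fairly detailed. At stake is some precision: intervals a little wider than they need be and a test a little less powerful. How much depends on whether site acts on the quantity that the planned contrast estimates, and this has to be checked for the two-visit model as described.

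**Working it through.** **Inputs from the Protocol article.** Two sites; 1:1 allocation stratified by site; two visits; random intercept; treatment contrast = group-by-time; 98 participants; 30% expected attrition; assumed treatment effect 0.50 (Sample Size). The site split reproduces: 35/58 = 60.3% and 23/58 = 39.7%.

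**Assumptions, not in the documents.** Within-person correlation ρ of 0.3 to 0.7; site difference in mean change δ of 0 to 0.5 SD of the outcome; equal sites, as the plan intends.

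**Step 1: a constant site difference.** With two visits, the group-by-time estimate is essentially the between-arm difference in within-person change. If one site scores higher by the same amount at both visits, that amount subtracts out of every participant's change.

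A simulation confirms this (98 participants, 49 per site, outcome SD 1, ρ = 0.5, no treatment effect, 100 to 150 replicates per scenario, dropout completely at random, random intercept per participant). Mean standard error of group-by-time:

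| Site difference in level | Dropout | No site term | Site main effect added |
|---|---|---|---|
| 0.5 SD | 0% | 0.2018 | 0.2018 |
| 1.0 SD | 0% | 0.2026 | 0.2026 |
| 0.5 SD | 30% | 0.2332 | 0.2328 |
| 1.0 SD | 30% | 0.2306 | 0.2289 |

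The two columns agree with complete data and differ by less than 1% with 30% dropout (0.2306/0.2289 = 1.007). A bare site main effect therefore gains almost nothing.

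**Step 2: a site difference in change.** With outcome SD 1, the within-site variance of a change score is 2(1 − ρ). If mean change differs by δ between two equal sites, omitting site adds δ²/4 to the residual variance. The ratio of nominal to true standard error is

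sqrt(1 + (δ²/4) / (2(1 − ρ))) = sqrt(1 + δ²/(8(1 − ρ))).

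| δ (SD) | ρ = 0.3 | ρ = 0.5 | ρ = 0.7 |
|---|---|---|---|
| 0 | 1.000 | 1.000 | 1.000 |
| 0.2 | 1.004 | 1.005 | 1.008 |
| 0.3 | 1.008 | 1.011 | 1.019 |
| 0.5 | 1.022 | 1.031 | 1.051 |

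Worked example for the largest entry: 0.25/(8 × 0.3) = 0.104, and sqrt(1.104) = 1.051. In sample-size terms that is 1 − 1/1.104 = 9% of the information. At ρ = 0.5 it is 1 − 1/1.0625 = 6%. With the current 35:23 split, the factor 1/4 becomes 35 × 23/58² = 0.239, so the figures barely move.

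The simulation with 30% dropout and ρ = 0.5 agrees. Adding site plus site-by-time lowers the mean standard error from 0.2352 to 0.2333 at δ = 0.3 (ratio 1.008) and from 0.2381 to 0.2317 at δ = 0.5 (ratio 1.028).

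**Step 3: scale.** A δ of 0.5 SD means that the sites differ in change by as much as the whole treatment effect assumed for the sample size. The upper end of the table is therefore generous.

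**Step 4: error rate.** With no treatment effect, the model without site rejected in 3% to 7% of replicates. That is compatible with 5% at this number of replicates, where the Monte Carlo standard error is about sqrt(0.05 × 0.95/150) = 1.8 percentage points. Nothing suggests inflation.

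**The case against.** The strongest case against the point has three parts.

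First, this is a condensed article. Statistical Methods says which terms the models will include and does not say that there are no others. Data Management and Safety Monitoring says that the analysis plan is still to be finalised, and adjustment covariates are often settled there. This stands as far as it goes: the list cannot be read as exhaustive, and nothing in the article rules site out. It does not dispose of the point, because the same section goes as far as the covariance structure and the effect-size measure while leaving out the one factor that shaped the allocation.

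Second, a constant site difference cancels from the planned contrast, so the omission may cost nothing. This stands in full. The loss is conditional on change differing by site, and no figure in the documents bears on that. The 35 to 23 split is a count during recruitment and says nothing about outcome differences.

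Third, any error is on the conservative side. This also stands: the omission does not threaten the type I error rate.

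**Conclusion.** The mismatch is real and minor. Allocation is stratified by site, and the model terms as named do not include it. The consequence is a standard error for group-by-time that is about 0–5% too large, assuming a site difference in change of 0 to 0.5 SD, a within-person correlation of 0.3 to 0.7 and roughly equal sites. It is nil, or nearly so, if the sites differ only in level. Precision is affected; validity is not.

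A reader might infer more than the documents support:

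- **That the analysis ignores its design and will give standard errors that are too wide.** This is not established. It needs a site difference in change, for which the article gives no evidence.
- **That leaving out site biases the treatment contrast through unequal loss across sites and arms.** The article reports only that 46 of 58 enrolled participants completed, with no breakdown by site or arm, so this is speculation.
- **That the sites must differ because separate local teams run them.** The article divides staff into blinded and unblinded units and does not describe staffing by site.

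**What to change.** State in the analysis plan that study site (two levels, fixed) enters the primary models in a form that can act on the post score. Either of these would do:

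- if the two-visit mixed model is kept, add site and site-by-visit; a site main effect alone would name the factor but leave the standard error essentially unchanged;
- if a baseline-adjusted ANCOVA of the post score is used instead, add site as a covariate.

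Neither calls for a treatment-by-site interaction.

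The cost is about one degree of freedom in the treatment comparison, out of roughly 98 × 0.7 ≈ 68 participants with both visits at the expected attrition. Site is already known for every participant, so no new data are needed. The article puts the end of data collection at October 2026 and holds the dataset locked until the plan is final, so the sentence can be added before anyone sees results by arm.
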